## Abstract

**Background:**

Endovascular treatment options for the superficial femoral artery are evolving rapidly. For long lesions, the venous femoropopliteal bypass considered to be superior above the prosthetic bypass. An endoluminal bypass, however, may provide equal patency rates compared to the prosthetic above knee bypass. The introduction of heparin-bonded endografts may further improve patency rates. The SUrgical versus PERcutaneous Bypass (SuperB) study is designed to assess whether a heparin-bonded endoluminal bypass provides equal patency rates compared to the venous bypass and to prove that it is associated with improved quality of life, related to a decreased complication rate, or not.

**Methods/design:**

Two-hundred-twenty-two patients with peripheral arterial occlusive disease, category 3-6 according to Rutherford, will be randomized in two treatment arms; 1. the surgical femoro-popliteal bypass, venous whenever possible, and 2. the heparin-bonded endoluminal bypass. The power analysis was based on a non-inferiority principle, with an effect size of 90% and 10% margins (alpha 5%, power 80%). Patients will be recruited from 5 teaching hospitals in the Netherlands during a 2-year period. The primary endpoint is primary patency and quality of life evaluated by the RAND-36 questionnaire and the Walking Impairment Questionnaire. Secondary endpoints include secondary patency, freedom-from-TLR and complications.

**Discussion:**

The SuperB trial is a multicentre randomized controlled trial designed to show non-inferiority in patency rates of the heparin-bonded endograft compared to the surgical bypass for treatment of long SFA lesions, and to prove a better quality of life using the heparin bonded-endograft compared to surgically treatment, related to a reduction in complications.

## Background

In the treatment of long lesions of the superficial femoral artery (SFA) the surgical venous bypass is considered the gold standard [1]. Bypass surgery, however, is associated with complications and a prolonged hospital length of stay. Endovascular techniques have advanced and provided new treatment options for peripheral vascular disease, but may also induce complications as shown in the Basil trial [2]. Last few years evidence has been accumulating that the treatment of long lesions with (covered) stents may provide acceptable short- and midterm primary patency rates, as summarized in several recent reviews [3-7].

Randomized trials have shown that 1-year patency rates of self-expanding nitinol metal stents vary between 70-90% as recently summarized by Lin et al [5]. Despite improvements in stent design and introducer sizes, one of the major issues limiting patency is in-stent re-stenosis. It was recently demonstrated that with the use of covered stents, re-stenosis is reduced to edge stenosis only [8]. The efficacy of an ePTFE-covered nitinol stent (Viabahn, W.L. Gore, Flagstaff, AZ, USA) in treating chronic SFA long lesions, of over 8 cm length, is currently being compared to bare nitinol stents in a multicentre randomized controlled trial (VIBRANT trial). The study hypothesis is that the use of ePTFE-covered nitinol stents will result in greater mid-term (24 months) and long-term (36 months) patency. Although interim analysis has shown no significant differences at one-year, final results have to be awaited. Recently, the 4-year's results of a randomized trial have been published comparing an ePTFE-covered nitinol stent with the above-knee ePTFE femoropopliteal bypass [9]. The 1-year and 2-year patency rates were 73% and 74%, and 63% and 64%, respectively [10,11] At 4-years of follow-up, the primary patency rates were 59% and 58%, respectively and limb salvage rates were also comparable. When compared to a prosthetic bypass, however the venous bypass has better patency rates, with 1-year and 4-year primary patency rates of 87% and 70%, respectively. There are patient groups with long lesions of the SFA, including patients with severe co-morbidities, who might benefit from a less invasive treatment strategy. The risk of wound complications, limb edema, loss of the great saphenous vein, and cardiac complications may have to be taken into account when deciding to treat surgically or endovascularly.

Heparin-bonded prosthetic bypass grafts have shown improved patency rates in animal models and non-randomized clinical trials [12-14]. Recently, the heparin-bonding technology has been integrated within the Viabahn stentgraft. Using this technique results may further improve to the level of the current gold standard; the venous femoropopliteal bypass. Advantages of the endoluminal technique would be related to its minimal invasive character: less pain, earlier recovery and less early complications. To date, no studies have been performed to compare the use of heparin-bonded stent grafts for the treatment of long lesions of the SFA. The current study has been designed to compare the use of heparin-bonded stent grafts for the treatment of long lesions of the SFA to the venous surgical femoropopliteal bypass in a multicentre randomized controlled trial.

## Methods and design

### Study design

The design of the study is a multicentre prospective randomized controlled trial comparing the patency of the heparin-bonded endograft to the venous surgical bypass. Endpoints are primary patency after 1, 2 and 5 years, complications and quality of life.

### Study objectives

The aim of the study is to demonstrate that the heparin-bonded endograft provides equal patency rates compared to the venous surgical femoro-popliteal bypass. In addition we hypothesize that patients receiving a heparin-bonded endograft show better quality of life at 30-days compared to patients who were surgically treated.

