### Sample size calculation

The assumption has been made that the heparin-bonded endoluminal bypass will have a similar cumulative primary patency at one year compared to the venous bypass. For a non-inferiority trial with an effect size of 90% and a margin of 10%, 111 patients per group are needed (alpha 5%, power 80%). The effect size of 90% refers to an estimated patency rate at one year in the surgical control arm.

The assumption has been made that the heparin-bonded endoluminal bypass will have an increase in QOL, as measured by a 10-point increase in the SF-36 score, at 30 days follow-up. With a standard deviation of 20, 63 patients per group are needed (alpha 5%, power 80%).

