## Discussion

The aim of the present randomized trial is two-fold. First, it aims to compare patency rates of the endoluminal bypass, combined with the heparin-bonded technology, with the current gold standard, the venous femoro-popliteal bypass, the current gold standard. Second, it aims to demonstrate that an endovascular approach is associated with fewer complications and thus an improved quality of life. In order to have sufficient power, the trial was designed using a non-inferiority principle.

Data analysis will be performed in both an intention-to-treat as a per-protocol manner. The first will be performed to compare the endoluminal bypass with common surgical practice, namely that some patients will not have a vein usable for the bypass and that some endoluminal procedures will be converted to open surgery. The per-protocol analysis will give information about the performance of the endoluminal bypass itself.

There are several differences between the SuperB trial and previously published randomized trials [9,16]. The SuperB trial is the first trial using a heparin-bonded endograft and the inclusion criteria are chosen much broader since hybrid procedures, such as a reconstruction of the common femoral artery, are allowed. Moreover, the anti-platelet regime and the use of statins are standardized. The wide inclusion criteria are chosen because they mimic common surgical practice and thereby they reduce the risk on inclusion problems as was the case in the Scandinavian trial [16].

With the introduction of the heparin-bonded technology in the endograft the design of the stent has also been changed. The proximal edge of the endograft has no longer a straight, but a contoured edge (Figure 1). This adaptation will reduce infolding in case of oversizing, thereby maintaining laminar blood flow and preventing intimal hyperplasia and thus edges stenosis. The expected effect of the new endograft may therefore not only be attributed heparin-bonding technology.

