**Figure 1 F1:**
[figure not shown]
**The Viabahn endograft (W.L. Gore, Flagstaff, AZ, USA) with a contoured proximal edge**.

The SuperB trial hypothesizes that the treatment of the long lesion of the SFA with a heparin-bonded endograft will show equal patency rates compared to the surgical bypass, but a better quality of life for treatment with the heparin-bonded endograft is expected, related to a reduced morbidity. Therefore, patients will be asked to fill out the RAND 36 questionnaire before treatment and at each visit during follow-up. Patients with intermittent claudication additionally will be asked to fill out the Walking Impairment Questionnaire at the same visits. Trials on endoluminal bypass including quality of life scores have not been performed, to date.

In conclusion, the SuperB trial is a multicentre randomized controlled trial designed to show equality in patency rates of the heparin-bonded endograft compared to the surgical bypass for treatment of longer lesions of the SFA, but to show better quality of life using the heparin bonded-endograft compared to surgically treatment, related to a reduction in complications.

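### The stated aim and the closing conclusion promise equal patency, but the trial was sized for non-inferiority within 10 points, and a pass cannot show equality

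*Protocol article*

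**What the plan says.** The protocol article describes the patency claim in two ways.

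**Equality.** Study objectives states: "The aim of the study is to demonstrate that the heparin-bonded endograft provides equal patency rates compared to the venous surgical femoro-popliteal bypass". The last part of the Discussion gives equal patency as the trial's hypothesis, and its final paragraph describes the trial as "designed to show equality in patency rates of the heparin-bonded endograft compared to the surgical bypass". The Background of the abstract is looser and poses a question: the trial is "designed to assess whether a heparin-bonded endoluminal bypass provides equal patency rates compared to the venous bypass".

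**Non-inferiority.** Sample size calculation states: "For a non-inferiority trial with an effect size of 90% and a margin of 10%, 111 patients per group are needed", with alpha 5% and power 80%. It explains that the 90% is the estimated one-year patency in the surgical arm, and it assumes similar patency with the endograft. The abstract's Methods/design section repeats the non-inferiority basis, with the 10% margin in the plural. The abstract's Discussion calls the trial "designed to show non-inferiority in patency rates of the heparin-bonded endograft compared to the surgical bypass". The opening paragraph of the main Discussion adds: "In order to have sufficient power, the trial was designed using a non-inferiority principle".

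**The concern.** Non-inferiority and equality are different conclusions. A non-inferiority test asks whether the new treatment can be shown not to be worse by the margin or more. It leaves smaller deficits open and sets no limit in the other direction. Exact equality cannot be demonstrated by any finite trial. The nearest testable version is equivalence, which needs both a lower and an upper bound.

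The article attaches its power to non-inferiority but announces equality in its objective and in its conclusion, the two places that define what the trial may claim. The abstract's Discussion and the closing paragraph of the main Discussion are close to the same sentence, one with non-inferiority and the other with equality. A reader who follows the objective as written would report a non-inferiority pass as proof that the endograft has the same patency as the gold standard.

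**Working it through.** **Inputs**
- Control one-year primary patency 90%, margin 10%, alpha 5%, power 80%, 111 per group: Sample size calculation.
- Endograft patency 90%, so a true difference of zero: taken from the assumption of similar patency in the same section.
- Inferred, not printed: an absolute margin of 10 percentage points and a one-sided 5% test. Both are adopted because they reproduce 111.

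**Step 1. Reproduce the plan's figure.** For non-inferiority with unpooled variance,

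n per group = (z₁₋α + z₁₋β)² × 2p(1 − p) / margin²

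- One-sided 5%: (1.645 + 0.842)² × 0.18 / 0.01 = 111.3, matching the printed 111.
- One-sided 2.5%: (1.960 + 0.842)² × 0.18 / 0.01 gives 142 after rounding up, which does not match.

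**Step 2. Power at 111 per group for the claim that was sized.**

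- SE = √(2 × 0.9 × 0.1 / 111) = 0.0403
- Power = Φ(0.10 / 0.0403 − 1.645) = 79.9%; exact binomial enumeration of the Wald rule gives 80.3%.

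The printed 80% is therefore correct for non-inferiority.

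**Step 3. What a pass shows.** The sized rule, read as a lower confidence limit above −10 points, excludes a deficit of 10 points or more. With the planned standard error it can be met with an observed deficit of about 0.100 − 1.645 × 0.0403 = 0.034, or 3.4 points. By the normal approximation, the chance of a pass at a true deficit d is Φ((0.10 − d)/SE_d − 1.645), where SE_d = √{[0.09 + (0.9 − d)(0.1 + d)]/111}:

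| True deficit | Chance of a pass |
|---|---|
| 0 points | 80% |
| 2 points | 60% |
| 5 points | 30% |
| 10 points | 5% |

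These are ordinary properties of a 10-point non-inferiority design and no fault in it. They show only that a pass is compatible with patency that is not equal.

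**Step 4. Illustration only: an equivalence test.** The article gives no upper bound. If one assumes symmetric bounds of ±10 points, two one-sided tests and 90% patency in both arms, power at 111 per group is 2Φ(0.10/SE − z) − 1:

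| Level per side | Power by formula | Exact enumeration | n per group for 80% |
|---|---|---|---|
| 5% | 2 × 0.799 − 1 = 59.8% | 60.7% | 155 |
| 2.5% | 39.9% | 41.3% | 190 |

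The spread from about 40% to about 60% shows how far any equivalence power depends on choices that the article does not make.

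**The case against.** The strongest reply is that *equal* is shorthand. Wherever the design is specified, in the sample size section, two parts of the abstract and the opening of the Discussion, the article says non-inferiority. It plans no equivalence test. The abstract's Background asks a question and does not promise a demonstration. Study objectives is also not the only statement of aims, since the opening of the Discussion gives them again. And a condensed article may leave the formal hypothesis and reporting rule to the full protocol or analysis plan.

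Much of this stands. Non-inferiority is probably what was meant, and the abstract's Background is the mildest of the three places.

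A reader might infer more: that the trial's real power is about 60%, not 80%, or that 155 patients per group are needed. The documents do not support that. Those figures need an upper bound of +10 points and a level per side that appear nowhere in the article, and the printed 80% is explicitly tied to non-inferiority. Nor is it a defect in itself that a pass leaves deficits below 10 points open; that holds for any trial with this margin, and at a true 10-point deficit a pass occurs only about 5% of the time.

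The reply does not remove the contradiction. Both terms are printed, so condensation does not explain it, and the objective and the conclusion are where the permitted claim has to be exact.

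**Conclusion.** The concern holds as a mismatch between the announced claim and the sized claim. The objective, and the hypothesis and conclusion at the end of the Discussion, are wrong as written, because a 10-point non-inferiority design cannot show equal patency. The sample size and its power are not wrong: 111 per group gives 79.9% for non-inferiority, given a one-sided 5% level, 90% patency in both arms and an absolute 10-point margin. The first and last of these are inferred from the arithmetic, as is the confidence-limit form of the rule.

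What is at stake is the wording of the trial's main conclusion. A pass would support the statement that one-year patency is not worse by 10 points or more, and nothing stronger. The equivalence figures in the working are illustrations under assumed bounds and say nothing about the power of the trial as designed.

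**What to change.** - In Study objectives, in the hypothesis and conclusion at the end of the Discussion, and in the abstract's Background, replace *equal* and *equality* with: *non-inferior in one-year primary patency, i.e. not worse by 10 percentage points or more*. Leave each place's description of the comparator as it is, so that the edit does not change whether venous or surgical bypass is named.
- In the abstract's Methods/design, write *10-percentage-point margin* in the singular.
- State that meeting the margin will be reported as non-inferiority with its confidence interval, and not as equal patency.

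This needs no extra patients, data or change in sample size. The downside is a weaker permitted headline claim.

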### Sample size calculation

The assumption has been made that the heparin-bonded endoluminal bypass will have a similar cumulative primary patency at one year compared to the venous bypass. For a non-inferiority trial with an effect size of 90% and a margin of 10%, 111 patients per group are needed (alpha 5%, power 80%). The effect size of 90% refers to an estimated patency rate at one year in the surgical control arm.

The assumption has been made that the heparin-bonded endoluminal bypass will have an increase in QOL, as measured by a 10-point increase in the SF-36 score, at 30 days follow-up. With a standard deviation of 20, 63 patients per group are needed (alpha 5%, power 80%).

### Setting

Patients will be recruited from the following centers: Rijnstate Hospital, Arnhem; Isala Klinieken, Zwolle; Nij Smellinghe Hospital, Drachten; Antonius Hospital, Sneek; University Medical Center Groningen, Groningen, The Netherlands. In each of the participating centers, each surgeon performing the endovascular procedure must have placed at least ten endoluminal bypasses prior to treating patients who participate in the SuperB trial to prevent a learning curve bias.

The total study duration will be 7 years; the recruitment period will take 2 years and thereafter patients will be evaluated yearly until 5 years post-procedure.

### Primary endpoints

The primary endpoints of the study are the primary patency at 1-year follow-up. In addition the quality of life, using the RAND SF36 Questionnaire will be evaluated as a primary endpoint.

### Secondary endpoints

1. Secondary patency

2. Complications

3. Clinical improvement

4. Surgical and endovascular re-interventions

5. Target lesion revascularization

Additionally an exploratory, thus hypothesis generating, subgroup-analysis will be performed.

- Patients with disabling intermittent claudication (Rutherford 3) will be analyzed separately using pain-free and maximal walking distance and the Walking Impairment Questionnaire as additional endpoints.

- Patients with ischemic rest pain and necrosis (Rutherford 4-6) will be analyzed using major amputations as an endpoint.

### Ethical considerations

A patient who meets the entry criteria is fully informed about the trial and provided with a patient information and consent form. Patients willing to participate in the study are included after signing the informed consent form. This study is conducted in accordance with the principles of the Declaration of Helsinki and Good Clinical Practice guidelines. The study is approved by the Medical Ethics committee of Nijmegen (CMO 2010-089) and the local institutional board of each participating center.

### Safety and quality control

#### Data Safety Monitoring Board

The Data Safety Monitoring Board (DSMB) will review safety and makes recommendations regarding the conduct of the study to the steering committee and to the accredited Medical Ethical Board (METC) that approved the study protocol. An interim safety analysis will be performed at 1-year after initiation of the trail. This analysis will include at least 40 patients.

#### Adverse and severe adverse events

Adverse events (AE) are defined as any undesirable experience occurring to a participant during the study, whether or not considered related to the investigational device. This definition includes events occurring during hospital stay up to 30 days of follow-up. Underlying disease that was present at the time of enrollment is not reported as an AE, but any increase in the severity of the underlying disease will be reported as an AE. All AEs will be monitored from the time of enrolment through the 30-day follow-up visit. AEs will be recorded on the case record forms (CRFs). A description of the event, including the start date, end date, action taken, and the outcome will be provided.

A severe adverse event (SAE) is any event leading to death, major amputation or definitive graft failure.

Data on AEs will be reported to the DSMB and to the accredited METC via "Toetsingonline" on the website of the Central Committee on Research involving Human Subjects (CCMO, ccmo.nl).

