• Graft failure: Definitive occlusion of the bypass with unsuccessful thrombolytic or surgical treatment

• Re-intervention: Secondary percutaneous or surgical intervention of the bypass.

• Seroma - Non-infected fluid accumulation under the wound

• Hematoma - Accumulation of blood postoperatively in the operated area.

• Re-bleed - Accumulation of blood postoperatively requiring operative treatment.

• Abscess - Accumulation of pus in the operated area.

• Infected wound - Red, swollen, but closed wound, not requiring surgical drainage.

• Open wound - Non infected wound leaking fluid.

• Loss of sensibility - Postoperative clinical loss of sensibility of the skin in the operated leg.

• Femoral nerve damage - Clinical femoral nerve damage.

• Graft infection - Proven graft infection requiring long term use of antibiotics or graft removal.

• Edema - Postoperative persistent edema of the operated leg.

• Serious adverse event (SAE): An adverse event that leads to death or serious deterioration in the health of the subject, defined as death, definite failure of graft/bypass or major amputation in the treated leg

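### Adverse event monitoring closes at 30 days and serious events are defined as adverse events, so read literally later deaths, major amputations and graft failures are not reported as serious events in a 5-year trial

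*Protocol article*

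**What the plan says.** In the Protocol article, the section Adverse and severe adverse events opens with a broad definition: "Adverse events (AE) are defined as any undesirable experience occurring to a participant during the study". The next sentence brings in a time limit: "This definition includes events occurring during hospital stay up to 30 days of follow-up". The section then states that "All AEs will be monitored from the time of enrolment through the 30-day follow-up visit". Adverse event data are to be sent to the data safety monitoring board (DSMB) and to the ethics committee; no other data flow to either body is described.

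Serious events appear twice. The safety section says "A severe adverse event (SAE) is any event leading to death, major amputation or definitive graft failure", with no time window. The Definitions section says "Serious adverse event (SAE): An adverse event that leads to death or serious deterioration in the health of the subject", and then limits this to death, definite graft or bypass failure, or major amputation in the treated leg. Graft failure is defined there as "Definitive occlusion of the bypass with unsuccessful thrombolytic or surgical treatment".

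Under Data Safety Monitoring Board, the DSMB has a general remit to review safety, and "An interim safety analysis will be performed at 1-year after initiation of the trail", in at least 40 patients. Under Follow-up, visits with duplex ultrasound run to 5 years and all primary and secondary endpoints are registered.

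**The concern.** An SAE is defined as a kind of adverse event, and all adverse event monitoring stops at the 30-day visit. Followed as written, the SAE record of each patient therefore closes at 30 days as well. Death, major amputation and definitive graft failure can all occur at any time in the 5 years of follow-up, and they are the events for which a DSMB in a device trial is convened. The interim safety analysis comes at 1 year, when some patients will have many months of follow-up, but the only data described as reaching the DSMB would cover about the first month of each.

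There is also a gap in the definition. Graft failure requires an unsuccessful treatment, so a definitive occlusion that nobody tries to reopen is not graft failure on the wording, and hence not an SAE at any time.

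**Working it through.** **1. The wording, step by step.**
- Adverse event, general definition: any time during the study, which follows patients to 5 years.
- Adverse event, monitoring: enrolment to the 30-day visit. This conflicts with the general definition.
- SAE: an adverse event of a listed kind (Definitions). On a literal reading it takes the 30-day window.
- Reported to the DSMB and ethics committee: adverse event data.

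**2. What else would capture each component after day 30.**

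| Component | As an SAE after day 30, read literally | Other route in the article |
|---|---|---|
| Death | no | not a listed primary or secondary endpoint |
| Major amputation | no | exploratory endpoint, Rutherford 4-6 only |
| Graft failure after failed treatment | no | primary patency, re-intervention |
| Definitive occlusion, never treated | no, and not before day 30 either | primary patency |

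The secondary endpoint of complications might take in deaths and amputations, but the article neither says so nor gives it a time window.

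**3. How much could fall after day 30.** The article gives no rate or timing for death, amputation or definitive graft failure. The only usable figures are for primary patency. They overstate device failure, because loss of primary patency includes any stenosis with a peak systolic velocity ratio above 2.5. They serve here only to illustrate timing.

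Inputs: 222 patients in total; planned 1-year patency of 90% (Sample size calculation); and 73%, the lower of the two 1-year rates cited for a covered stent and a prosthetic bypass (Background). The plan's own figure reproduces: at one-sided 5% and 80% power, n = 2 × 0.9 × 0.1 × (1.645 + 0.842)² / 0.1² = 111.3 per group, against 111 stated. Nothing in this point changes that number.

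With S the 1-year patency and x = 30/365.25 = 0.0821, the proportion lost by day 30 is F = 1 − S^(x^k). Here k = 1 is a constant hazard and k = 0.5 a strongly front-loaded Weibull hazard. Both shapes are assumptions.
- S = 0.90, k = 1: F = 0.0086, or 1.9 of 22.2 first-year losses (8.6%).
- S = 0.90, k = 0.5: F = 0.0297, or 6.6 of 22.2 (30%).
- S = 0.73, k = 1: F = 0.0255, or 5.7 of 59.9 (9.5%).
- S = 0.73, k = 0.5: F = 0.0862, or 19.1 of 59.9 (32%).

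So about 68% (100 − 32) to 91% (100 − 8.6) of first-year losses come after day 30. For the cited venous bypass (87% at 1 year, 70% at 4 years), F = 0.0114 with k = 1 and 0.0391 with k = 0.5. Divided by the 4-year loss of 0.30, these give 4% and 13% of 4-year losses by day 30.

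**The case against.** The strongest reply is that the text is ambiguous, not a decision to leave late events unreported. The SAE sentence in the safety section has no window, the general definition covers the whole study, and the sentence with the 30-day limit says that the definition includes early events, which need not exclude later ones. The DSMB's remit is general, and its interim analysis is not limited to 30-day data. The article is also a condensation, and SAE reporting periods often sit in a full protocol or a DSMB charter. Part of this stands: that the DSMB would miss late events is an inference from the only data flow described. It does not remove the point, because the article does state a closing date for all adverse event monitoring and does define an SAE as an adverse event. The defect lies in what is written.

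A reader might infer more than the documents support:
- *The complications comparison is confined to 30 days and so favours the endograft.* The Discussion says that "it aims to demonstrate that an endovascular approach is associated with fewer complications", but Study design and Secondary endpoints give complications no window, endpoints are registered over follow-up, and data are analysed at 1, 2 and 5 years. Truncation would follow only if complications came from adverse event records alone, which is not stated.
- *Late occlusions are lost to the trial.* They are not. Duplex at every visit captures them as patency outcomes; the gap is in safety reporting.
- *Every SAE component is a long-term event.* Each can also occur before day 30.
- *The 10% to 27% losing patency by 1 year, 11 to 30 patients per arm, are device failures.* They are losses of primary patency, including stenosis.
- *Re-bleed and graft infection escape reporting because they are not SAEs.* Within 30 days they are adverse events and go to the DSMB and ethics committee as such.

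**Conclusion.** The point holds in a limited form. The safety section contradicts itself on when an adverse event can occur. Together with the Definitions, its literal reading ends SAE reporting at the 30-day visit. The consequence is greatest for death and major amputation, which have no firm alternative route after day 30, and less for occlusion, which is still measured as patency. The separate gap for untreated definitive occlusion follows from the wording alone.

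The figure of 68% to 91% of first-year losses after day 30 indicates only that most such events would lie outside the window even with a strongly front-loaded hazard. It rests on assumed hazard shapes and on primary patency as a proxy. The number of SAEs affected cannot be derived from the article. Sample size and the primary analysis are untouched. This is an inexpensive improvement to safety reporting, not a flaw in the main comparison.

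**What to change.** Reconcile the safety section with the Definitions:
- State that the SAE components already listed are recorded and reported to the DSMB and the ethics committee from enrolment to the end of follow-up.
- Word graft failure for this purpose so that it includes definitive occlusion whether or not treatment was attempted.
- Use one SAE definition in both places. At present one section says severe and the other serious, and only the Definitions restrict amputation to the treated leg.
- Keep the 30-day window, stated as such, for non-serious adverse events.
- Report the complications endpoint at both 30 days and 1 year, so that it cannot rest on 30-day adverse event records alone.

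The cost is revised wording and a small extra reporting burden at visits that are already scheduled. No additional patients, visits or imaging are needed.
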